# Trial Objectives and Purpose

## Mucosal immunity:

- To compare baseline mucosal immunity (through different methods) among three age groups with several degrees of protection acquired through immunization:
  - Infants 6-11 months of age will have received a few OPV doses
  - Children 5-6 years of age will have received multiple OPV doses in campaigns and are expected to have the highest levels of mucosal and humoral immunity
  - Children 10-11 years of age will not have received booster OPV doses for > 5 years. They are expected to have high antibody titers but may have waned mucosal immunity.
- To determine whether one dose of bOPV or IPV significantly reduces excretion of poliovirus types 1 and 3, respectively, following a challenge dose with bOPV, compared to an unvaccinated control arm.
- To determine whether one dose of bOPV or IPV significantly increases sIgA in crevicular fluids and stool samples, and to examine whether the increase in specific SIgA in these specimens is correlated to a reduction in excretion of Sabin poliovirus types 1 and 3 following the challenge with bOPV. This will allow evaluating the use of sIgA as a surrogate test for assessment of mucosal immunity.
- To determine the robustness of the mucosal immune response by study arm and age group, by measuring poliovirus antibody-secreting cells in an ELISPOT-spot assay 7 days after the administration of the study vaccine.

Humoral immunity:

- To determine whether one dose of bOPV or IPV will significantly increase seroprevalence and booster antibody titers compared to unvaccinated children.
- To assess whether one dose of IPV will significantly increase seroprevalence and antibody titers compared to a single dose of bOPV.
- To examine the correlations between antibody titers in blood and shedding of poliovirus after a challenge dose, for each vaccine study arm and age group.
- To examine the correlation between levels of IgA in serum and levels of secretory IgA in crevicular fluids and stool samples, before and after the booster vaccine dose, to gain further understanding on the mechanisms of mucosal immunity against poliovirus.
- To analyze correlations between levels of secretory IgA in crevicular fluids and stools and the ELISPOT test results, to better understand mucosal immunity against poliovirus.

Safety:

- To assess adverse events following vaccine administration.

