## A diagram of the study design is shown below.

## A specific statement of primary and secondary endpoints:

The primary endpoint is reduction in excretion at days 3,7 and 14 post- challenge dose of vaccine poliovirus administered 28 days after a single dose of bOPV or IPV.

The secondary endpoints are:

- Increase of sIgA in gingival fluids and stools 28 days after a dose of bOPV or IPV.
- Increase in poliovirus antibody secreting cells (measured with ELISPOT) 7 days following a dose of bOPV or IPV.
- Seroconversion or antibody titer boosting 28 days following a single dose of bOPV or IPV.

A description of what kind of trial:

This is a randomized controlled unblinded trial.

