# Assessment of Efficacy

## Specification of the efficacy parameters:

Humoral immunity: Sera collected at study entry (day 0) and during the 7-, 28- and 56-day visits, will be examined for the presence (detectable) or absence of neutralizing antibodies to all three poliovirus serotypes. A reciprocal titer of 8 is considered to indicate the presence of neutralizing antibodies. In addition, a change from non-detectable (reciprocal <8) to detectable (reciprocal >8), or from below the highest dilution tested (reciprocal <1448) to the highest dilution tested (reciprocal >1448) will also indicate seroconversion. Although highest titre for neutralizing antibodies is 1024, we are taking end point dilution of half a log higher then 1024. This log of 10.5 is the highest observable titre and is being used because of high titres observed in this highly immunized population.

For participants with detectable antibodies, antibody boosting is defined as a >4-fold increase.

Mucosal immunity: Stool specimens will be collected at 0, 28, 31, 35 and 42 day visits. The samples will be examined for the presence or absence of polioviruses and other enteroviruses. In positive samples, the virus type will be determined following standard protocols from the World Health Organization (WHO) [20]. In addition, the amount (titration) of virus particles will be measured in those samples positive for poliovirus.

Semi-quantitative levels of sIgA in gingival fluid and stool samples will be determined using ELISA. High, medium and low levels will be determined and correlated in each study subject with serum antibody levels and with virus shedding after the challenge (Annex VIII-IX).

Additionally, in a subset of children 10-11 years of age, blood samples collected on days 0 and 7 will be tested to detect the amount of antibody-secreting lymphocytes specific for poliovirus using the ELISPOT technique.

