1. Add 490µl MEM 2% FBS to 70µl heat inactivated test sera aliquots (for a final dilution of 1:8).
2. Add 25µl MEM 2% FBS to rows B-H of the test plates with multichannel pipette.
3. Add 25µl MEM 2% FBS to each row of back titration plates (S1, S2 and S3).
4. Add 50µl MEM 2% FBS to every well of the cell control plate.
5. Add 50µl MEM 2% FBS of each serum dilution (1:8) to row “A” only of the test serum plate (3 well/serum dilution and 4 test sera per plate – see figure).
6. Repeat this procedure for the poliovirus type 2 and type 3 test serum plates.
7. Make serial 2-fold dilutions with Cetus dilutor from row A through row H (serum dilutions will range from 1:8 to 1:1024).
8. Dilute each poliovirus serotype in MEM 2% to contain 100 TCID50 according to figure below. Prepare sufficient virus challenge suspension for the number of sera to be tested; each plate requires approximately 2.5ml of diluted challenge virus.
9. Prepare the back titrations of each poliovirus serotype in MEM 2% FBS. Titrate each virus from 100 TCID50 a further three 10-fold steps. (see figure below)
10. 10.

| **Virus Stock** In Hep2-C | Aliquoted 08/09/99 | | | 1000µl/vial | |  |  |
| --- | --- | --- | --- | --- | --- | --- | --- |
| **Sabin 1** 100 TCID50 = 10-5.2 |  |  | | 100 | 10 | 1 | 0.1 |
| virus 633µl 100µl | 100µl | 100µl | 800µl  5.4ml 45ml | 7ml | 100µl | 100µl | 100µl |
| medium 367µl 900µl | 900µl | 900µl | 7.2ml | 63ml | 900µl | 900µl | 900µl |
| **Sabin 2** 100 TCID50 = 10-5.35 |  |  |  |  |  |  |  |
| virus 448µl 100µl | 1004µl | 100µl | 800µl  5.4ml 45ml | 7ml | 100µl | 100µl | 100µl  f |
| medium 552µl 900µl | 900µl | 900µl | 7.2ml | 63ml | 900µl | 900µl | 900µl |
| **Sabin 3** 100 TCID50 =10-5.0 |  |  |  |  |  |  |  |
| virus 100µl | 100µl | 100µl | 800µl  5.4ml 45ml | 7ml | 100µl | 100µl | 100µl  _ |
| medium 900µl | 900µl | 900µl | 7.2ml | 63ml | 900µl | 900µl | 900µl |

1. Add 25µl of 100 TCID50 of relevant poliovirus antigen to all wells in the test serum plates.
2. To the back titration plates:

- Add 25µl of 100 TCID50 of virus to rows A and B (*i.e*., 24 wells/dilution)
- Similarly, add 25µl of the next three 10-fold dilutions to rows C and D, E and F, and G and H, respectively.

1. Wrap all plates in plastic wrap and tap gently to mix. Incubate for 3 hours at 36°C and 5% CO2.

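### Boosting is scored in every child with detectable antibody, but under the 1448 titre ceiling a rise of more than four-fold cannot be recorded from a day-0 titre of 362 or more

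*Protocol*

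**What the plan says.** The humoral definitions stand in the Protocol under Assessment of Efficacy, Specification of the efficacy parameters.

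- Detectable antibody: "A reciprocal titer of 8 is considered to indicate the presence of neutralizing antibodies".
- Boosting: "For participants with detectable antibodies, antibody boosting is defined as a >4-fold increase". No upper limit is set on the day-0 titre.
- Ceiling: "Although highest titre for neutralizing antibodies is 1024, we are taking end point dilution of half a log higher then 1024", and "This log of 10.5 is the highest observable titre and is being used because of high titres observed in this highly immunized population". The serology annex agrees on the range of the plates: "serum dilutions will range from 1:8 to 1:1024".
- Seroconversion is a change from undetectable to detectable, "or from below the highest dilution tested (reciprocal <1448) to the highest dilution tested (reciprocal >1448) will also indicate seroconversion".

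The secondary humoral endpoint joins the two: "Seroconversion or antibody titer boosting 28 days following a single dose of bOPV or IPV". Under Trial Objectives and Purpose, the children of 5-6 years "are expected to have the highest levels of mucosal and humoral immunity", those of 10-11 years are also expected to have high titres, and the infants will have had only a few OPV doses.

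**The concern.** A four-fold criterion needs room above the starting titre. The Protocol raised its endpoint because it expects many titres near the top of the assay, then applied the criterion to every seropositive child. A child who starts too close to the ceiling is counted as not boosted whatever the true response.

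Two things are at stake. Within an age group, these children add non-responders to every arm and shrink the difference in boosting between vaccine and control. Across age groups, a boosting rate reported on its own would be lower where day-0 titres are higher, even if the vaccine effect were the same.

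**Working it through.** **1. The ceiling.** Half a log2 step above 1024 is 2^10.5 = 1024 × √2 = 1448.15. This reproduces the Protocol's 1448. (Half a log10 step would give 3238, so log2 is meant.)

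**2. The limit for boosting.** 2^10.5 / 4 = 2^8.5 = 362.04. The largest rise that can be recorded is 1448 divided by the day-0 titre:

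| Day-0 titre | Largest recordable rise |
|---|---|
| 256 | 5.66-fold |
| 362 | 4.00-fold |
| 512 | 2.83-fold |
| 724 | 2.00-fold |
| 1024 | 1.41-fold |
| 1448 | 1.00-fold |

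Boosting is strictly more than four-fold, so 362 itself already fails. If triplicate wells give steps of 1/3 log2 (an assumption), the highest titre from which boosting can be scored is 287. If at least four-fold were meant, 362 would qualify and the next step, 456, would not.

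**3. Routes to a response by day-0 titre, for a child with detectable antibody.**

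- Below 362: boosting, or the ceiling route.
- From 362 to below 1448: the ceiling route only. Read literally, >1448 can never be observed when 1448 is the highest observable titre, so there would then be no route at all.
- At 1448: none.

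**4. Illustration.** Assumed: true rise with mean 3 log2 (8-fold) and SD 1; assay SD 0.4 log2; readings in 1/3-log2 steps capped at 10.5; 400,000 simulated children per scenario. The ceiling route is read as reaching 1448.

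| | Day-0 mean log2 7, SD 2 | Day-0 mean log2 9, SD 1.5 |
|---|---|---|
| Share at 362 or more | 26% | 67% |
| Share at 1448 | 5% | 20% |
| Scored boosted, all detectable | 57% | 27% |
| Boosting or ceiling seroconversion | 76% | 71% |
| Scored boosted, day-0 titre below 362 | 77% | 80% |

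The rows agree with each other: 0.77 × (1 − 0.26) = 0.57, and 0.80 × (1 − 0.67) = 0.26, which is 27% up to rounding. Mean rises of 2.5 and 4 log2 show the same pattern for boosting alone (46% v 22%, and 70% v 32%).

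**5. Dilution between arms.** A second simulation used day-0 SD 1.5 log2, no assay error, and either an 8-fold mean rise or no mean rise. Differences between the two, in percentage points:

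| Day-0 median | Boosting alone | Boosting or ceiling seroconversion |
|---|---|---|
| 64 | 80.1 − 2.2 = 77.9 | 84.4 − 2.6 = 81.8 |
| 512 | 31.0 − 0.8 = 30.2 | 76.0 − 9.2 = 66.8 |
| 1024 | 13.4 − 0.4 = 13.0 | 58.8 − 10.2 = 48.6 |

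With no mean rise, the combined endpoint still scores 2.6% at a median of 64 and 10.2% at 1024, because a move from 1024 to 1448 (1.41-fold) counts as seroconversion.

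**6. Range.** Over assumed medians of 64, 256, 512 and 1024 (SD 1.5 to 2.0), the share of detectable children at 362 or more is 5-11%, 37-40%, 60-63% and 78-84%.

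**The case against.** The strongest reply is that the same paragraph already deals with the ceiling. A child who starts between 362 and 1448 and reaches the top counts as seroconverted, and the secondary endpoint accepts either seroconversion or boosting. Reading >1448 as at 1448 is reasonable, because the sentence describes it as the highest dilution tested. On that reading the 30-point gap in the illustration (57% v 27%) falls to 5 points (76% v 71%). This stands, and it limits the point largely to boosting as a separate quantity. It does not remove it: the ceiling route belongs to seroconversion, credits rises as small as 1.41-fold, and leaves children already at 1448 without a route.

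A reader might infer that the best-immunised age group will look least responsive whatever the vaccine does. The documents do not support that. They give no day-0 titres, the combined endpoint recovers most of the loss, and no section plans to compare boosting between ages: the humoral objectives compare arms, and the chi-square test by arm and age group is for seropositivity. Nor is the comparison of arms biased. Randomised arms within an age group share the same ceiling, so the effect is dilution.

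It can also be said that titres are compared by non-parametric tests in any case, and that denominators can be left to a statistical analysis plan, which may exist but is not shown. The first is true and limits the harm. The second does not apply here, because the Protocol itself fixes who is scored for boosting.

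**Conclusion.** The point holds as a defect in the definition of part of a secondary endpoint. That a rise of more than four-fold is unrecordable from 362 upwards is exact and needs no assumption beyond the Protocol's own ceiling. Its size is not known: it depends on day-0 titres that the Protocol does not give, and the unscorable share could lie anywhere from about 5% to 84% under the distributions tried. Boosting reported alone is capped and its arm differences are diluted. The combined endpoint is affected much less, provided that >1448 means at 1448. The primary endpoint, shedding after challenge, is untouched.

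**What to change.** In Specification of the efficacy parameters:

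- Define the boosting denominator, separately for each serotype, as children with a detectable day-0 titre below 362 (1448/4).
- Report, by arm and age group, the number at 362 or more and the number at 1448 on day 0.
- Report ceiling seroconversions separately from boosting, and correct >1448 to at 1448 or above. A child who starts below 362 and reaches 1448 meets both rules and should count once in the combined endpoint.
- Keep all children with a positive titre in the non-parametric titre comparison already planned in Annex II.

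Day-0 serum is drawn before vaccination, so restricting on it preserves the randomised comparison. The change is wording only. Its price is a smaller denominator, and so less precision, for the boosting proportion.

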**1. Introduction**

IgA and IgM antibody detection in serum specimens from children previously immunized with either inactivated poliovirus vaccine (IPV) or oral poliovirus vaccine (OPV) is necessary to determine a child’s immunization status in a post eradication era.

**ELISA test**: Wells of microtiter plates are coated with either goat anti-human IgA or goat anti-human IgM antibodies. After washing, wells are blocked with gelatinand human serum samples are applied and allowed to bind to the coating antibody. After washing off any unbound human sera, type-specific antigen is applied and allowed to bind to the serum antibodies. After washing off unbound antigen, type-specific mouse monoclonal antibody is added to detect bound antigen. After washing off unbound monoclonal antibody, peroxidase-labeled anti-mouse conjugate is added to detect bound type specific monoclonal antibody. After washing off unbound conjugate, the captured conjugate is then measured using a detection system employing TMB. The final reaction is stopped by adding a specific citric acid solution. Plates are then scanned by a spectrophotometer at 620nm and calculations are performed to determine the result.

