**3. Equipment and Supplies:**

a. Immulon 2HB, 96-well polystyrene, flat-bottom, high-binding. Thermo No: 3455 (Fisher cat . no: 14-245-61)

b. Bio-safety cabinet (Baker, Sterilguard III)

c. Incubator (Precision)

d. Multichannel Pipette (Gilson 50-200 ul)

e. Pipettes: (Gilson LTS 2ul, 10 ul, 20 ul, 200 ul, 1000 ul)

f. Deep well dilution racks (VWR)

g. 15 ml and 50 ml centrifuge tubes (Falcon)

h. 2 ml, 5 ml, 10 ml, and 25 ml serological pipettes (Falcon)

i. Reagent reservoirs (Costar)

j. Scale (Ohaus, Adventurer)

k. Stir plate (Thermolyne)

l. Freezers at -20oC and -70oC

m. Refrigerator +4oC

n. ELISA washer (SKATRON, ScanWasher300)

o. ELISA reader (TECAN SPECTRAFluor Plus spectrophotometer)

4. Procedure:

Coat the capture antibody onto the solid phase of a microplate

a. Using a multichannel pipette, coat labeled 96-well microplates with 50 ul/well of a 1:500 dilution of goat anti-human IgA in Carbonate Buffer. (50ug/well)

b. Using a multichannel pipette, coat labeled 96-well microplates with 50 ul/well of a 1:500 dilution of goat anti-human IgM in Carbonate Buffer. (50ug/well)

c. Incubate the microplates for 60 minutes, 37oC (plates flat in moist chamber,not stacked).

d. Wash the plates 4X with wash buffer. (Tap plates on a paper towel to remove residual liquid).

Addition of blocking buffer

e. Using a multichannel pipette, add 200 ul of P-G-T/well.

f. Incubate the microplates for 60 minutes, 37oC (plates flat in moist chamber, not stacked).

g. Wash the plates 4X with wash buffer. (Tap plates on a paper towel to

remove residual liquid).

Addition of serum

h. Using a multichannel or single-channel pipette, add 50 ul of a 1:200 dilution in P-G-T of each positive-control serum, negative-control serum, and test serum, vertically across the microplate to the appropriate wells. (Test serum in columns 1 and 2, 3 and 4, 5 and 6, 7 and 8, 9 and 10, 11and 12).

i. Incubate the microplates for 90 minutes, 37oC (plates flat in moist chamber,

not stacked).

j. Aspirate serum, fill wells with wash buffer and allow plates to soak for 3 minutes. Aspirate wash buffer, fill wells with wash buffer and allow plates to soak for an additional 3 minutes. Wash the plates 4X with wash buffer. (Tap plates on a paper towel to remove residual liquid).

Addition of type specific antigen

k. Using a multichannel pipette, add 50 ul of a 1:20 dilution in P-G-T of each antigen to the appropriate plates and wells. (Antigen in columns 1-12, rows A-H).

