l. incubate the microplates overnight at room temperature (plates flat in moist chamber, not stacked).

m. As pirate serum, fill wells with wash buffer and allow plates to soak for 3 minutes. Aspirate wash buffer, fill wells with wash buffer and allow plates to soak for an additional 3 minutes. Wash the plates 4X with wash buffer. (Tap plates on a paper towel to remove residual liquid).

Addition of type specific monoclonal antibodies

n. Using a multichannel pipette, add 50 ul of a 1:40000 dilution in P-G-T of each MoAb to the appropriate plates and wells. (MoAb in columns 1-12,rows A-H).

o. Incubate the microplates for 90 minutes, 37oC (plates flat in moist chamber, not stacked).

p. As pirate serum, fill wells with wash buffer and allow plates to soak for 3 minutes. Aspirate wash buffer, fill wells with wash buffer and allow plates to soak for an additional 3 minutes. Wash the plates 4X with wash buffer. (Tap plates on a paper towel to remove residual liquid).

Addition of horseradish peroxidase labeled conjugate

q. Using a multichannel pipette, add 50 ul of a 1:5000 dilution in P-G-T of goat anti-mouse IgG (H&L) horseradish peroxidase labeled conjugate. (HRP conjugate in columns 1-12, rows A-H))

r. Incubate the microplates for 90 minutes, 37oC (plates flat in moist chamber, not stacked).

s. Aspirate serum, fill wells with wash buffer and allow plates to soak for 3 minutes. Aspirate wash buffer, fill wells with wash buffer and allow plates to soak for an additional 3 minutes. Wash the plates 4X with wash buffer. (Tap plates on a paper towel to remove residual liquid).

Addition of SureBlue ReserveTM Substrate

t. Using a multichannel pipette, add 50 ul of SureBlue ReserveTM Substrate previously warmed to room temperature. (Substrate in columns 1-12, rows A-H).

u. Incubate the microplates for 15 minutes undisturbed at room temperature.(plates flat, not stacked).

Addition of TMB BlueStopTM Solution

v. Using a multichannel pipette, add 50 ul of TMB BlueStopTM Solution previously warmed to room temperature. (BlueStopTM in columns 1-12 rows A-H).

w. Read absorbance of each plate 10 minutes post-addition of the BlueStopTM Solution using a 620 nm filter.

Figure 1:

|  | 1 | 2 | 3 | 4 | 5 | 6 | 7 | 8 | 9 | 10 | 11 | 12 |
| --- | --- | --- | --- | --- | --- | --- | --- | --- | --- | --- | --- | --- |
| A | Pos. Control | Pos. Control | Spec. 6 | Spec. 6 | Spec. 14 | Spec. 14 | Spec. 22 | Spec. 22 | Spec. 30 | Spec. 30 | Spec. 38 | Spec. 38 |

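### sIgA is reduced to high, medium and low before it is correlated with serum antibody and shedding, although the ELISA described gives a numeric reading that rank methods could use

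*Protocol*

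**What the plan says.** Under Assessment of Efficacy, the protocol's specification of the efficacy parameters states: "Semi-quantitative levels of sIgA in gingival fluid and stool samples will be determined using ELISA". The next sentence fixes what enters the analysis: "High, medium and low levels will be determined and correlated in each study subject", the comparators being serum antibody and post-challenge shedding. No cut-offs for the three levels are given there or in the annexes.

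The ELISA is set out in Annex VIII. Its introduction says "Plates are then scanned by a spectrophotometer at 620nm and calculations are performed to determine the result", and its last step is "Read absorbance of each plate 10 minutes post-addition of the BlueStopTM Solution using a 620 nm filter". The annex is written for serum at one dilution: "add 50 ul of a 1:200 dilution in P-G-T of each positive-control serum, negative-control serum, and test serum". It gives no dilution series or standard curve.

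The sIgA result is used in two ways. One secondary endpoint is "Increase of sIgA in gingival fluids and stools 28 days after a dose of bOPV or IPV", with no scale stated. Trial Objectives and Purpose asks whether the rise in sIgA goes with reduced excretion, so that sIgA can be judged as a surrogate test. Annex II, which the Statistics section names as the analysis plan, uses non-parametric tests for serum titres and for the amount of virus excreted. It does not mention sIgA.

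**The concern.** An absorbance is numeric and ordered, even if it is only semi-quantitative. With three levels, all children within a level are treated as equal and the ordering among them is lost. An association with titre or shedding is then harder to detect. If a product-moment correlation is computed on scored levels, it is also pulled towards zero. A useful surrogate could look weaker than it is, and a search for surrogates is one of the trial's declared reasons for collecting these specimens.

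There is also a conditional problem. If the same three levels were used for the day 0 to day 28 increase, a child in the top level at day 0 would have nowhere to go. The protocol expects children aged 5-6 years to have the highest mucosal immunity of the three age groups, so they might be the most exposed.

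**Working it through.** **Is there a figure to reproduce?** No. The protocol gives no sIgA cut-off, standard deviation, target correlation or power. Everything below rests on stated assumptions.

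**What the text fixes.** The three levels are the only sIgA scale named for the correlations. The section on efficacy parameters points to Annexes VIII-IX for sIgA, and the section on methods and timing points to Annexes VII and VIII. Annex VII is the neutralisation test and Annex IX is the ELISPOT procedure, so Annex VIII is the only ELISA available to read. Its output is numeric.

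**Information kept by three levels.** Assume that the reading X is standard normal (after a log transform if needed) and linearly related to the comparator. Let c1 and c2 be the cuts, with levels scored T = 0, 1, 2 and shares p0, p1, p2. Then

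- Cov(X, T) = φ(c1) + φ(c2)
- Var(T) = p1 + 4·p2 − (p1 + 2·p2)²
- share kept = Cov² / Var(T); the correlation is multiplied by its square root.

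*Equal thirds:* c = ±0.4307 and φ = 0.3636. Cov = 0.7272, Var = 0.6667, share kept = 0.5288 / 0.6667 = 0.793.

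*10/20/70:* c1 = −1.2816 and c2 = −0.5244. Cov = 0.1755 + 0.3477 = 0.5232, Var = 0.44, share kept = 0.2737 / 0.44 = 0.622.

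| Assumed shares, low/medium/high | Loss of information | Correlation multiplied by | 89 children count as about |
| --- | --- | --- | --- |
| 27/46/27 (smallest loss) | 19.0% | 0.900 | 72 |
| equal thirds | 20.7% | 0.891 | 71 |
| 20/30/50 | 24.4% | 0.869 | 67 |
| 10/20/70 | 37.8% | 0.789 | 55 |
| 5/15/80 | 49.0% | 0.714 | 45 |
| 5/90/5 | 57.5% | 0.652 | 38 |

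The 89 is the protocol's completer number per arm and age group (Annex I). It is used here only to give scale.

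**Against a rank correlation.** A rank correlation on the full reading has asymptotic efficiency 0.912 under normality. With equal thirds, 0.793 / 0.912 = 0.870, a loss of about 13%. At 10/20/70, 0.622 / 0.912 = 0.682, a loss of about 32%.

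**Binary shedding.** In a simulation with n = 89 and 3,000 runs, the log-odds of shedding were −1.0 at average sIgA and fell by 0.75 per SD. Power was 86% with the numeric reading against 77% with equal thirds, and 85% against 64% with 5/15/80. The numeric arm used a product-moment correlation, so a rank test would gain somewhat less.

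**If the levels also governed the increase.** Suppose every child rose by 0.5 SD. The share moving up a level would be 35% with equal thirds, 30% at 20/30/50 and 21% at 10/20/70.

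**The case against.** The strongest objections, and what stands of each:

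- **The endpoint.** A reader might infer that the sIgA secondary endpoint cannot register a rise in the children expected to be highest. The text does not support that. It attaches the levels to the correlations only. The endpoint and the objectives speak of an increase without a scale, and that detail may properly sit in a statistical analysis plan that is not shown. Even if the levels applied, only children already in the top level would be affected. The 5-6 year group is described as highest relative to the other ages, not as falling in a high ELISA category. This objection stands, so the point is conditional.
- **The size.** A reader might take one fifth as the established loss. It needs normality and near-equal groups, and it is measured against the full reading rather than against the rank method proposed here. This stands too: only an assumed range can be given.
- **The assay.** Annex VIII is a serum assay at a single dilution. It describes no preparation or control for stool or crevicular fluid, and absorbance may saturate. Broad levels are a defensible way to report such an assay. This limits the gain and rules out calling the change free of cost. It does not justify discarding order, because rank methods need nothing more than order, which a semi-quantitative reading supplies.
- **Bias.** Attenuation towards zero is a property of a product-moment coefficient on scored levels. The protocol names no coefficient, so loss of precision is the safer description.

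**Conclusion.** The point holds in a limited form. The protocol states a three-level category as the quantity to be correlated, the one ELISA it describes yields a numeric reading, and nothing in the document says that the reading itself will be analysed. For a normal marker, the loss is about 19-21% of the information with near-equal groups. With equal thirds it is about 13% against a rank correlation. It is larger when most children share a level, reaching 38% at an assumed 10/20/70 split and 19-58% over the splits tabulated. The cut-offs and the true distribution are unknown, so none of these is a property of the plan as written.

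The effect on the increase endpoint is conditional on the same levels being used there. The damage is to the surrogate-marker and correlation objectives. The primary shedding comparison, its test and the sample size are not touched.

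**What to change.** In the specification of the efficacy parameters, make the ordered ELISA reading the analysed quantity, normalised to an assay control suited to the specimen. Then state:

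- Spearman correlation of the reading with serum titres and with the quantity of virus shed;
- a rank test of the reading between shedders and non-shedders;
- a rank test by arm of the change from day 0 to day 28, saying in advance whether change is a difference or a ratio, because the ranking of changes depends on that choice.

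Keep high, medium and low for description only, with cut-offs fixed before the data are seen. This follows the non-parametric approach that Annex II already takes for titres and virus quantity.

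The cost is a change of wording and a little more analysis; no further specimens are needed. A control appropriate to stool and to crevicular fluid has to be identified, because the annex shows only serum controls. Readings that saturate at the single dilution will be tied at the top, so only part of the lost information may be recovered.
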